#### Secondary endpoints

##### Efficacy

Rate of plan deliverabilityRate of plan acceptability on blinded review of dose distributions

##### Acceptability

Stakeholder evaluation (patients, ROs, medical radiation therapists (MRTs), physicists) using a Likert scale modeled on the Theoretical Framework of Acceptability (version 2) [22]

##### Scalability

Completion of the Intervention Scalability Assessment Tool (ISAT) [23] by stakeholders for submission to program leads

## Study design

This will be a pragmatic, randomized, controlled, open-label, feasibility trial.

All study activities will take place at the London Regional Cancer Program in London, Ontario, Canada.

Patients will be randomized in a 1:2 ratio between the current standard treatment workflow (Arm 1) and the experimental treatment workflow (Arm 2).

Patients will be stratified by treatment target volume. Group 1 will include bone and soft tissue metastasis targets, and Group 2 will include primary or metastatic intrathoracic disease targets.

## Patient selection

Potential study participants may be identified/screened by a member of the study team or any staff RO, and patients who meet inclusion/exclusion criteria will be eligible for recruitment. Potential participants will receive a verbal explanation of the study by a study team member/RO, receive a paper Letter of Information/Consent, and be given the opportunity to discuss the trial/ask questions with the Collaborating Investigator.

Potential participants who feel comfortable signing consent at this initial encounter will be allowed to do so, but reminded of their right to withdraw their consent at any time and for any reason.

Potential participants who would like additional time to review the LOI and/or discuss things with their care partners will be encouraged to do so. This additional consideration time is clinically reasonable given that these patients would generally receive treatment within 7-14 days of consult, and because any oncologic emergency requiring immediate intervention would exclude the patient from participation. Potential participants will be informed that the Collaborating Investigator will follow-up with them via telephone within 2-3 business days, but that they are free to contact the Collaborating Investigator sooner if they make a decision. Those who wish to participate will be given the option to complete an electronic consent form prior to their first radiation appointment, or to complete the form with the Collaborating Investigator at a separate appointment (scheduled in advance of the treatment day).

### Inclusion criteria

#### Patient inclusion criteria

Age 18 years or olderAble to provide informed consentPatient has consented to PRT to bone/soft tissue metastases or primary targets in the thorax, abdomen or pelvis and RO will use simple planning techniques (i.e. parallel-opposed pair or direct field beam arrangement)Patient will be scheduled for same day simulation and treatment (if randomized to Arm 1)Patient has a pre-existing and recent (i.e. within 4 weeks of time of enrollment) diagnostic CT or CT-fused scan with full visualization of the region-of-interest which has been acquired from an approved diagnostic scanner (CT scans must have been performed within 4 weeks [28 days] of the date of trial enrollment to minimize the risk of significant interval radiographic change [s]).Patient positioning for diagnostic scan is deemed acceptable and reproducible (e.g., patient is lying supine and relatively flat, there is no/minimal motion blur, etc.)Intravenous (IV)/oral contrast in the region-of-interest is permitted as long as it does not create artifact which obscures the target volume (density override calculations may be required)

#### Clinician inclusion criteria

Age 18 years or olderAble to provide informed consentParticipation in the workflow of an arm 2 patient in the capacity of Radiation Oncologist, Medical Physicist, or Medical Radiation Technologist (Therapy)

### Exclusion criteria

#### Patient exclusion criteria

Any contraindication to receiving radiationOncologic emergencies and/or on-call casesPregnant or lactating womenCases requiring composite dosimetric planning to account for previous radiotherapy or extended distance set-upAny contraindication to receiving radiation

#### Clinician exclusion criteria

None

## Pre-treatment evaluation

Eligibility according to inclusion and exclusion criteriaHistory and physical examination

## Treatment schema

Please see Fig. 1. For detailed treatment planning and delivery information, please see Section 8.

**Fig. 1 Fig1:**
[figure not shown]
DART trial schema

## Registration and randomization

All study data will be entered into REDCap; an electronic case report form database. De-identified supporting source documents will be uploaded directly into REDCap.

### Registration and randomization procedure

Login to REDCap, add a new record and a study number will be automatically generated.Complete the Enrollment Form in REDCap. Upload the de-identified consent form and signed Statement of Eligibility.If the participant meets all the eligibility criteria, complete the Randomization form.

## Treatment plan

The electronic booking action form (EBAF) will be completed *after* randomization. ROs must specify “DART” and indicate the trial arm to facilitate bookings. For Arm 2 patients, the EBAF must specify the diagnostic image set to be imported for planning.

### Arm 1: conventional workflow

#### Scheduling

Patients will be booked for CT simulation and treatment as per the local institution’s standard practice.

#### CT simulation

As per local standard practice.

#### Target/organ-at-risk contouring

ROs must generate, at minimum, a planning target volume (PTV) contour. Organs-at-risk (OARs) may be contoured at the RO’s discretion to guide multileaf collimators (MLC) shielding, but optimization objectives are not allowed.

#### Dose and fractionation

All palliative dose/fractionation schemes are eligible to a maximum total dose of 30 Gy and a maximum of 10 fractions.

#### Planning and QA

Patients in Arm 1 will undergo simple palliative planning and QA as per the local institution’s standard practice. Plans will include no more than two fields and will not employ beam modification devices aside from MLCs.

#### Treatment delivery

##### Immobilization and set-up

As per local standard practice.

##### Image guided radiotherapy

*A CBCT must be performed for image-guidance at fraction 1*. Subsequent image-guided radiation therapy (IGRT) is at the discretion of the treating RO/radiation therapists in the context of local imaging protocols.

### Arm 2: experimental workflow

#### Scheduling

Patients randomized to Arm 2 *do not* require a CT simulation appointment. A radiation treatment appointment will be scheduled on an optical surface guidance-equipped treatment unit as soon as available, but a minimum of 24 hours is required between EBAF processing and fraction 1. Arm 2 patients must be scheduled between 10:00 am and 4:00 pm. The treating RO must be on-site and available by pager during the treatment appointment.

#### CT simulation

CT simulation is not required, but the remainder of the patient care pathway, including CT-related activities, will still apply. Instead of a simulation, CT staff will import the specified diagnostic image set and then complete tasks as per standard practice.

#### Target/organ-at-risk contouring

ROs must generate, at minimum, a PTV contour. OARs may be contoured at the RO’s discretion to guide MLC shielding, but optimization objectives are not allowed.

#### Dose and fractionation

All palliative dose/fractionation schemes are eligible to a maximum total dose of 30 Gy and a maximum of 10 fractions.

#### Planning and QA

Patients in Arm 2 will also undergo simple palliative planning and QA as per the local institution’s standard practice. Plans will include no more than two fields and will not employ beam modification devices aside from MLCs.

Treatment unit QA will include importing an external contour DICOM structure into VisionRT.

#### Treatment delivery

##### Immobilization and set-up

A full-body Vaclok bag, which has been shaped to replicate the curve of diagnostic machine couch tops, is required. Using optical surface guidance, unit therapists may use available pillows, cushions, headrests and other passive immobilization devices as required to closely (within a predefined tolerance) reproduce patient set-up in the region-of-interest. Once an acceptable set-up has been achieved, unit therapists will document the set-up instructions in the electronic chart. Optical surface guidance is to be used for subsequent set-ups, though non-permanent skin markings are also allowed.

##### Image guided radiotherapy

*A CBCT must be performed for image-guidance at fraction 1*. A surface reference must be captured after shifts have been applied. Subsequent IGRT is at the discretion of the treating RO/radiation therapists in the context of local imaging protocols.

The treating RO, clinical specialist radiation therapist, and/or medical physicist should be paged to review the image match if there are any concerns.

##### Undeliverable plan

Plans may be deemed undeliverable in the following scenarios:The treatment position could not be reproduced within tolerance *and* there is significant anatomical or external contour variation that cannot be corrected with IGRTProgression has occurred such that the target volume requires expansion for adequate coverageChanges are observed on CBCT that contraindicate PRTCBCT reveals new findings such as interval development of pathological fracture, atelectasis, etc. which warrant PRT deferral for further assessment or involvement of other services

At the discretion of the RO, CBCT-enabled planning may be enacted if a diagnostic-CT-enabled plan is considered undeliverable. This process is described in the next section.

##### Treatment delivery with CBCT plan

If the treating RO decides to engage this process, a DART-team medical physicist will be paged to the unit immediately to import/register/prepare the CBCT acquisition for planning. While the plan is generated, the patient can stay on the treatment bed or wait in the unit waiting area. The RO will re-contour the target on the CBCT and delineate field borders/shielding. The medical physicist will generate a simple plan for immediate RO approval and perform the required physics QA. A unit therapist will then perform new case QA. The patient can then be treated using the CBCT plan after repeat CBCT for verification.

## Subject discontinuation/withdrawal

Subjects may voluntarily discontinue participation in the study at any time. If a subject is removed from the study, the clinical evaluations that would have been performed at the end of the study should be obtained.

## Data collection and evaluation of efficacy, acceptability, and scalability

### Efficacy

#### Primary endpoint: time in centre (TIC)

TIC is defined as the total time in hours spent at the cancer centre and will be measured as follows:*Arm 1*: Scheduled CT simulation appointment time to time of beam delivery completion.*Arm 2*: Scheduled radiation treatment appointment time of beam delivery completion.

If machine/technical/patient-related delays or other unforeseen circumstances cause a delay to appointment time of more than 15 minutes, start time will be recorded and an adjusted TIC will be calculated based on the actual appointment start time. The intention of the adjusted TIC is accurate capture of TIC under normal operating conditions.

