### Endpoints

#### Primary endpoints

The primary endpoint is time in centre (TIC) on the treatment day. This is defined as the total time in hours spent at the cancer centre from the scheduled CT simulation (Arm 1) or treatment delivery (Arm 2) appointment until beam delivery completion.

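### The adjusted TIC removes a late treatment unit in Arm 2 but not in Arm 1, and the plan does not say whether adjusted or unadjusted TIC is tested

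*Protocol article*

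**What the plan says.** The Protocol article, *Primary endpoints*, measures TIC "from the scheduled CT simulation (Arm 1) or treatment delivery (Arm 2) appointment until beam delivery completion". The section *Primary endpoint: time in centre (TIC)* repeats this by arm. For Arm 1 it gives "Scheduled CT simulation appointment time to time of beam delivery completion", and for Arm 2 "Scheduled radiation treatment appointment time of beam delivery completion".

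The same section then adds an adjustment with a broad trigger. Where machine, technical or patient-related delays, or other unforeseen events, "cause a delay to appointment time of more than 15 minutes, start time will be recorded and an adjusted TIC will be calculated" from the actual start of the appointment. The purpose is stated: "The intention of the adjusted TIC is accurate capture of TIC under normal operating conditions".

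Under *Patient inclusion criteria*, "Patient will be scheduled for same day simulation and treatment (if randomized to Arm 1". Every Arm 1 patient is thus meant to have a treatment-unit appointment inside the TIC window, after simulation and planning.

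*Statistical analysis plan* compares TIC between arms with a two-sample t-test, or a Wilcoxon rank sum test if the data are not normal. It does not mention adjusted TIC.

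**The concern.** The adjustment is worded identically for both arms, but it acts on a different appointment in each. In Arm 2 the clock starts at the treatment unit, so a late unit moves the start of the clock and the delay disappears. In Arm 1 the clock starts at CT simulation. A late unit then falls between start and stop and is counted, and nothing in the document subtracts it.

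The rule therefore misses its own aim. If adjusted TIC is meant to describe a day without unusual delay, it does so for start delays in Arm 2 and for simulation delays in Arm 1, but not for treatment-unit delays in Arm 1. At stake are the size of the time saving credited to the experimental workflow and the error rate of the only primary test. The section also creates two versions of the primary endpoint, and the analysis section does not choose between them.

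**Working it through.** **Reproducing the plan's figure.** The inputs, from *Sample size calculation*, are means of 4.8 and 2.5 h (difference 2.3 h), SD 2 h, a two-sided t-test at 0.05, 80% power, 1:2 allocation and 10% dropout. The noncentral t solution is 9.59 control patients, or 3 × 9.59 = 28.8 in total. Then 28.8 / 0.9 = 31.96, which rounds up to 33 for a 1:2 split. The stated 33 (11 and 22) is reproduced. Power is 0.818 with 10 + 20 patients evaluable and 0.855 with 11 + 22.

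**What the rule does to each arm.** Let B₁ and B₂ be the delay-free durations, S a simulation start delay over 15 minutes (Arm 1 only), and U a treatment-unit start delay over 15 minutes. For simplicity, U has the same distribution in both arms and adds one-for-one to TIC.

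| | Arm 1 | Arm 2 | Expected difference, Arm 1 − Arm 2 |
|---|---|---|---|
| Delay-free target | B₁ | B₂ | E[B₁] − E[B₂] |
| Unadjusted TIC | B₁ + S + U | B₂ + U | E[B₁] − E[B₂] + E[S] |
| Adjusted TIC as written | B₁ + U | B₂ | E[B₁] − E[B₂] + E[U] |

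Two results follow.

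- Against the delay-free target, adjusted TIC overstates the Arm 2 saving by E[U].
- Against time actually spent in the centre (unadjusted TIC for a patient who arrives on time), the shift is E[U] − E[S]. Its sign cannot be known from the document.

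**Size.** The document gives neither the frequency nor the length of delays, so these are assumptions: 10–50% of patients with a qualifying unit delay, averaging 0.5–1.5 h. Then E[U] = share delayed × mean delay.

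- Low end: 0.10 × 0.5 = 0.05 h, and 0.05 / 2.3 = 2%.
- High end: 0.50 × 1.5 = 0.75 h, and 0.75 / 2.3 = 33%.

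**Effect on the test if adjusted TIC is used and there is no true difference.** SE = 2 × √(1/11 + 1/22) = 0.739 h, with 31 degrees of freedom. The two-sided rejection probability comes from the noncentral t with noncentrality bias / SE.

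| Assumed bias (h) | Share of 2.3 h | Bias / SE | Rejection probability |
|---|---|---|---|
| 0.05 | 2% | 0.07 | 5.0% |
| 0.25 | 11% | 0.34 | 6.2% |
| 0.30 | 13% | 0.41 | 6.8% |
| 0.50 | 22% | 0.68 | 10.1% |
| 0.75 | 33% | 1.02 | 16.6% |

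**Check by simulation** (8,000 trials per scenario, 10 vs 20 evaluable, exponentially distributed delay lengths). With 25% of patients delayed by a mean of 1 h, the rule as written rejects in 6.4% of trials; keeping unit delays in both arms gives 5.1%. With 50% delayed by a mean of 1 h, the figures are 9.4% and 4.9%. Treating unit delays alike in both arms restores the nominal rate.

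**The case against.** A reader might infer that the primary comparison is biased in favour of Arm 2, and always in that direction. The document does not support this, for two reasons.

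- **Direction.** The rule also removes simulation start delays from Arm 1. If the target is actual time in centre, this works against the Arm 1 penalty and may outweigh it. The abstract calls CT simulation a bottleneck. That may refer to scheduling rather than delay on the day, but nothing shows that simulation delays are negligible.
- **Which variable is tested.** TIC is defined from the scheduled time, adjusted TIC is a separately named quantity, and the analysis section names only TIC. Read literally, the test uses unadjusted TIC and the asymmetry never reaches it. The stated intention of the adjustment points the other way, so the text is ambiguous. An analysis plan that is not shown may settle the choice.

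Three further points limit the size. The top of the assumed range needs half of all patients to be delayed by an average of 1.5 h, under a rule meant for departures from normal operation. Some Arm 1 unit delay may overlap with planning still under way, since *Background* says the conventional process usually takes at least 4 hours; it would then not lengthen TIC one-for-one. And the trigger covers patient-related delay. For a late arrival, the adjustment rightly removes time not spent in the centre.

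These points limit the direction, reach and size of the problem. They do not remove the asymmetry from adjusted TIC: it follows from the two clock-start definitions together with same-day treatment in Arm 1.

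**Conclusion.** The point holds in a limited form. Adjusted TIC as written handles treatment-unit start delays differently by arm, and so misses its stated aim. Against that delay-free aim, it favours Arm 2 by the mean unit delay left in Arm 1. Against actual time in centre, the direction is unknown. The primary test is affected only if adjusted TIC is the analysed variable, which the article does not settle.

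The size rests wholly on assumed delays. Over 0.05 to 0.75 h the error rate runs from 5.0% to 16.6%, and it is about 6% at 0.25 h. These figures also assume a constant shift, an unchanged SD of 2 h and 11 vs 22 patients analysed. Rare or short delays would make the effect negligible, and even the top of the range is only a third of the planned 2.3 h difference. This is a worthwhile correction to the definition of the sole primary endpoint. It is not evidence that the planned result would be an artefact.

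**What to change.** State in *Primary endpoint: time in centre (TIC)* and in *Statistical analysis plan* that the primary test uses unadjusted TIC, with the same start rule in both arms. If arrival time is recorded, exclude in both arms the time before a late-arriving patient is present.

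Report adjusted TIC only as a sensitivity analysis. There, also subtract an Arm 1 treatment-appointment start delay of more than 15 minutes, so that unit delays are treated alike in both arms.

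The cost is wording plus recording the scheduled and actual start of the Arm 1 treatment appointment; the article does not say whether these times, or patient arrival, are already captured. Some operational noise will remain in the primary variable. The sample size need not change on this account.

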#### Plan deliverability

Plan deliverability will be reported as either yes or no. *Primary Plan Deliverability* will refer to the deliverability of the diagnostic-CT-enabled treatment plan. *Secondary Plan Deliverability* will refer to the deliverability of the CBCT-based plan in cases where a CBCT-based plan is generated.

For any undeliverable plan, the RO must document the reasons why the plan was undeliverable and the PI must be alerted within 24 hours.

#### Plan acceptability

Plan acceptability will be determined by blinded RO review, performed by an expert panel comprised of RO members from the local Palliative Disease Site Team. Because a review of the *planned* dose distribution would not preserve blinding due to visibly apparent characteristics of CT/CT simulation imaging, plan acceptability will be assessed by review of dose distribution of the *delivered* plan shown on the fraction 1 image matching CBCT.

Plan acceptability is defined according to the following local criteria for simple palliative planning:*For parallel-opposed pair plans:*Adequate (as per RO discretion) coverage of the target volume (PTV) by the 90% isodose lineHot spot (maximum point dose) is ≤115% of prescribed dose OR if hot spot is > 115% then the total volume of the hot spot should be <2cm^3^*For single direct field plans:*Adequate (as per RO discretion) coverage of the target volume (PTV) by the 80% isodose lineHot spot (maximum point dose) is ≤125% of prescribed dose OR if hot spot is > 125% then the total volume of the hot spot should be <2cm^3^

Blinded-reviewers will ascribe a score of 1, 2 or 3 to each plan based on the following criteria:AcceptableMinor deviation but still acceptableUnacceptable – plan deficiency may impact clinical outcome

Plan acceptability *does not* refer to clinical judgements such as target delineation, beam arrangement, energy, field borders, shielding, dose/fractionation, etc.

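### The fraction 1 CBCT used to blind the plan-acceptability review is acquired in a set-up that differs by arm, so the image may still reveal the arm

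*Protocol article*

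**What the plan says.** In the protocol article, Plan acceptability gives the scoring to a local panel: "Plan acceptability will be determined by blinded RO review, performed by an expert panel comprised of RO members from the local Palliative Disease Site Team". The same section explains that showing the planned dose "would not preserve blinding due to visibly apparent characteristics of CT/CT simulation imaging", and therefore "plan acceptability will be assessed by review of dose distribution of the *delivered* plan shown on the fraction 1 image matching CBCT".

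Both arms have that image. The Image guided radiotherapy sections for Arm 1 and Arm 2 each state: "A CBCT must be performed for image-guidance at fraction 1". The Immobilization and set-up sections differ:

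- **Arm 2:** "A full-body Vaclok bag, which has been shaped to replicate the curve of diagnostic machine couch tops, is required".
- **Arm 1:** "As per local standard practice".

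Study design makes this a single-centre trial: "All study activities will take place at the London Regional Cancer Program in London, Ontario, Canada". Under Treatment plan, the radiation oncologist (RO) records the trial arm on the booking form.

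The rating has two parts. Coverage of the target by a fixed isodose line (90% for parallel-opposed pairs, 80% for single direct fields) is judged adequate or not at the RO's discretion. The hot spot has numeric limits (115% or 125% of the prescribed dose, or a volume under 2 cm³ if exceeded). Each plan is scored 1, 2 or 3, and 3 means unacceptable.

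**The concern.** The protocol accepts that the look of an image can give away the arm, and it changes the image under review for that reason. The replacement image is acquired with the patient in the treatment position, and the prescribed support under the patient is not the same in the two arms. The step meant to remove an arm signal may therefore bring in another one.

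A second route does not depend on the image. The panel comes from the ROs of the only participating centre, and an RO who treated a trial patient knows that patient's arm.

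This matters because the Background section rests the evaluation of the workflow's efficacy on plan deliverability and plan acceptability, with pain or treatment response deliberately not chosen as an endpoint. Part of the acceptability score is discretionary, and blinding is meant to protect that part.

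**Working it through.** **The passages side by side**

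1. Image reviewed: the fraction 1 CBCT, in both arms (Plan acceptability).
2. When it is taken: at fraction 1, for image guidance, so with the patient in the treatment set-up (Image guided radiotherapy, both arms).
3. Set-up in that image: curved full-body bag required in Arm 2, local standard practice in Arm 1 (the two Immobilization and set-up sections).
4. From 1 to 3, the reviewed image is acquired under conditions that differ systematically by arm. Whether a reviewer can see the difference depends on the CBCT field of view, the review display and the devices used in Arm 1. The article describes none of these. The share of Arm 2 images that show the arm could be anything from 0% to 100%; this is an assumption range, not an estimate.
5. Reviewers: ROs of the local team at the single centre. The treating RO knows the arm from the booking form (Treatment plan). In Arm 2 the treating RO is also among those who may be paged to look at the fraction 1 image match if there are concerns (Image guided radiotherapy). The article does not say whether panel members also treat trial patients.

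**Which part of the score is exposed**

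- Coverage: the isodose line is fixed, but adequacy is a judgement, so it is exposed.
- Hot spot: numeric limits, so it is much less exposed.
- Target delineation, beam arrangement, field borders and the like are expressly outside the rating.

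**Scale**

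The concern rests on no figure stated in the plan. The only inputs are the planned group sizes, 11 and 22 (Sample size calculation). These reproduce with the exact two-sided t-test. For a difference of 4.8 − 2.5 = 2.3 h and SD 2, power is 77.3% at 9 + 18 and 81.8% at 10 + 20. That gives 30 evaluable patients, and 30 × 1.1 = 33.

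- Weight of one plan moved across the boundary between scores 2 and 3: 1/22 = 4.5 percentage points in Arm 2, 1/11 = 9.1 in Arm 1.
- The article gives no expected acceptability rates, so the rates below are assumptions. They show the chance that Fisher's exact test at 0.05, with 11 against 22 plans, finds a significant difference:

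| Arm 1 rate | Arm 2 rate | Chance of p ≤ 0.05 |
|---|---|---|
| 90% | 90% | 1.4% |
| 90% | 80% | 2.0% |
| 90% | 70% | 11.9% |
| 90% | 95% | 3.7% |
| 90% | 100% | 9.0% |

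A 10-point shift in Arm 2 is about 2 plans (0.10 × 22 = 2.2). In either direction it would seldom reach significance. Any distortion would therefore show mainly in the reported rate, and the planned test would not flag it.

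**The case against.** The strongest reply has three parts.

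**The leak is not shown.** Field of view, display and Arm 1 devices are not described, so the bag may lie outside the image, or Arm 1 may use something similar. This stands. A reader might infer that the review will in fact be unblinded; the article does not support that. It supports only that the image can reveal the arm.

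**The recusal part argues from silence.** A journal article condenses the protocol, and reviewers described as blinded should not include someone who planned the case. This stands in part. A reader might infer that panel members treat or recruit trial patients. However, Patient selection says only that any staff RO may identify or screen patients, and Arm 2 Scheduling says only that the treating RO must be on-site and reachable. Overlap at one centre is plausible but not documented. What remains is that blinding of the image cannot protect a case the reviewer already knows, so a stated rule is worth having.

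**Blinding is not the only safeguard.** Fixed isodose lines, numeric hot-spot limits, a panel, and the exclusion of clinical judgements all help, and calling a plan unacceptable is a high threshold. This stands, and it confines the concern to the coverage judgement. It is also tempting to cite the Limitations section as conceding bias in this endpoint. That passage concerns perceived burden, and a similar bias among clinicians who accrue; it does not discuss the plan review.

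**Conclusion.** The point holds as a possible weakness in the blinding of one secondary efficacy endpoint. The protocol relies on the fraction 1 CBCT to hide the arm, yet prescribes a different support under the patient in Arm 2 for that same image. The conclusion depends on two things the article does not state: whether the bag or the posterior surface it shapes is visible to reviewers, and whether a panel member may have treated the patient being scored.

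Neither the size nor the direction of any bias can be derived. The 4.5 points is the weight of one plan among 22 and should not be read as an estimate of bias. Only the discretionary coverage judgement is materially exposed. Time in centre, the primary endpoint, and the sample size of 33 are unaffected. This is a cheap improvement to make before the review starts, not a flaw that undermines the trial.

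**What to change.** Add the following to Plan acceptability:

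1. In both arms, before review, mask the CBCT and dose display outside the patient's external contour (couch, bag, cushions) and remove plan and treatment-unit identifiers.
2. State that a panel member does not score a patient they consulted on, contoured, approved or treated.
3. Have each reviewer record a guess of the arm for each plan, and report the guesses by arm. This is needed because masking does not hide a posterior body surface that has taken the bag's curve; the guesses show whether that residual cue mattered.

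The cost is slightly more preparation per case and less freedom in assigning reviewers within the existing panel. Treatment, sample size and the primary analysis do not change.
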